#### 2-mile run test

The 2_MR_ will be used as a continuous field test to assess CRF. It will be performed on a 400-m synthetic athletic track with the supervision of the research team. Participants will be required to complete the 2-mile run course without any physical help in the shortest time possible. At the start, all participants will line up behind the starting line. On the command “go,” the clock will start. They will begin running at their own pace. Although walking is authorized, it is strongly discouraged. Immediately after competition of the test, the time achieved will be reported to the nearest to 0.01 s and used for further analysis. The heart rate at the end of the 2-mile test will be considered the maximal heart rate achieved in the test. Additionally, the perceived effort of the trial will be recorded at the end of the test using the modified Borg visual scale (Borg, 1982).

#### 30-15 Intermittent fitness test

30-15_IFT_ test will be used as the field-based assessment tool to measure CRF, as previously recommended (Buchheit, 2008; Mohorič et al., 2021). This intermittent, incremental test consists of 30-s shuttle runs interspersed with 15-s active recovery periods. Running speed was set at 8 km/h for the first 30-s run and increased by 0.5 km/h in each 30-s phase thereafter. Participants will be required to run back and forth between two lines 40 m apart at the predetermined pace determined by a prerecorded beep. The prerecorded beep allowed participants to adjust their running speed when they entered a 3-m zone in the middle and at each end of the test field. During the 15-s recovery period, participants will walk to the nearest line (either in the middle or at the end of the running area, depending on where their previous run had ended); from this line, they began the next running phase. Participants will be instructed to complete as many stages as possible. The test ended when the participant could no longer maintain the required running speed or failed to reach the 3-m zone three consecutive times in time before the sound signal. The speed of the last successfully completed stage was recorded as the test result, i.e., the MRS during 30-15_IFT_ (MRS_IFT_) (Buchheit, 2008). The VO2max was calculated by following formula (ref):

$$V\,O_{2}\,m\,a\,x\,I\,F\,T\,\left(\frac{m\,l}{\frac{m\,i\,n}{k\,g}}\right)=28.3-2.15\,S-0.741\,A-0.0357\,B\,M+0.058\,A\times M\,R\,S_{I\,F\,T}+1.03\,M\,R\,S_{I\,F\,T}$$

Whereas (G) stands for sex, (A) for age and (BM) for subjects’ body mass, respectively.

#### Rating of perceived exertion

Before and after each session, the “Rating of Perceived Exertion” (RPE) scale was used to estimate the participants’ perceived effort. It ranged between 0/“no perceived effort” (i.e., rest) and 10/“maximal perceived effort” (i.e., the most stressful exercise ever performed) (Borg, 1982).

### Sample size calculation and statistical analysis

#### Sample size

In the conceptualization phase of the study, we conducted an *a priori* power analysis for the estimated interclass correlation coefficient (ICC) as previously recommended (Bujang and Baharum, 2017). Based on previous studies with similar aim we expected to find high to nearly perfect ICC for the reliability of 30-15_IFT_ test (Buchheit, 2008; Buchheit et al., 2011). Therefore, with power of 0.90, two-tiled α = 0.05, and four observations per subject a minimum sample size of 6 subjects showed to be sufficient to detect a value of ≥ 0.80 for the ICC.

#### Statistical analysis

All data will be presented as mean ± SD with 90% confidence interval limits (90% CI). All statistical analysis will be conducted using the SPSS statistical software (version 27.0, IBM Inc., Chicago, United States). Descriptive statistics will be used to summarize demographic characteristics of participants and outcomes. Normality od the data will be confirmed by using the visual inspection of histogram and Q-Q plot and analytically by Shapiro-Wilk test, while the homogeneity of variances of normally distributed variables will be tested by using Levene’s test.

Differences in key physiological outcomes between the different CRF tests (TR vs. 2_MR_ vs. 30-15_IFT_) will be assessed by One-Way ANOVA analysis. The relative reliability of all dependent variables between two 30-15_IFT_ trials will be estimated using the ICC, two-way random effects model (consistency type). ICC values will be classified as very high if > 0.90, high if between 0.70 and 0.89, and moderate if between 0.50 and 0.69. The following criteria will be used to declare good reliability: CV < 5% and ICC > 0.69 (Buchheit et al., 2011). In addition, the standard error of the estimate (SEM) and the coefficient of variation (CV) will be calculated as measures of absolute reliability, indicating the within-subject variation, as previously proposed (Hopkins, 2000). To further address the reliability of the data, bias and random error will be calculated, followed by the minimal detectable change (MDC). To test the usefulness of the IFT, the spreadsheet provided by Hopkins will be used (Hopkins). Usefulness will be determined by comparing the smallest worthwhile change (SWC) with the typical error of measurement (TE) and will be interpreted as follows: “Marginal” (TE > SWC), “OK” (TE = SWC) and “Good” (TE < SWC) (Hopkins, 2007).

Relationship between VO_2max_, HR_peak_ and end running speed of 30-15_IFT_, TR, and 2_MR_ will be assessed using Pearson’s correlation (r). Also, the relationship between VO_2max_ obtained from TR, 2_MR_, and 30-15_IFT_ will be investigated. The following thresholds of the correlation coefficient will be used to assess the magnitude of the relationships analyzed: weak ≤ 0.35; 0.36 ≤ moderate < 0.67; 0.68 ≤ high < 1 (Taylor, 1990).

In addition, to determine performance differences between two groups of SAF members, a repeated-measures General Linear Model will be used for main physiological parameters estimated from different tests (TR vs. 2_MR_ vs. 30-15_IFT_) as within-subject factor, whereas groups (HSG vs. LSG) will be used as between-subject factors. Partial eta squared (η^2^) values of 0.01, 0.06, and 0.14 rated difference as small, moderate and high, respectively (Cohen, 1988). Statistical significance for all analysis conducted will be accepted at *p* ≤ 0.05.

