**Methods and analysis:**

This randomized cross-over study using a within-subjects test-retest design will enroll 32 infantry members of the Slovenian Armed Forces. To investigate the reliability and validity of the 30-15_IFT_ test, an incremental treadmill test (TR), a 2_MR_ test, and two identical 30-15_IFT_ will be performed in randomized order. Additionally, participants will be subsequently divided into two groups based on their score on the Army Physical Fitness Test (APFT), whereas differences in visual attention will be assessed by using the d2 test. The primary analysis will assess differences in key physiological outcomes between the different CRF tests (TR vs. 2_MR_ vs. 30-15_IFT_). In addition, the relative reliability of all dependent variables between two 30-15_IFT_ trials will be estimated by interclass correlation coefficient (ICC), while relationship between maximal oxygen uptake, heart rate and maximal running speed of 30-15_IFT_, TR and 2_MR_ will be assessed using Pearson’s correlation.

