## Materials and methods

### Study design

The proposed study is a part of a greater project entitled “Enhancement of Physical and Combat Preparedness of Slovenian Armed Force Members; “(original language, Slo: “Dvig telesne in bojne pripravljenosti pripadnikov Slovenske vojske”), which was funded by the Slovenian Research Agency (ARRS) and Slovenian Ministry of Defense (project No. V5-2106; project manager: Assoc. [name]. [name]; principal investigator: Assist. [name]. [name]). This is a randomized cross-over study using a within-subjects test-retest design. To test the current hypothesis, an incremental treadmill test (TR), a 2_MR_ test, and two identical 30-15_IFT_ will be performed in the population of SAF soldiers. For a better understanding of the following text, the term participant is used instead of soldier. The present study will be conducted over a maximum period of 2 weeks per participant. Participants will be instructed to visit the laboratory four times at least 72 h apart. At the first visit, they will be familiarized with the experimental procedures and asked to sign a written informed consent form to participate in the study. Then, participants will be randomly assigned to four experimental conditions (i.e., TR, 2_MR_ and two 30-15_IFT_ running tests).

Additionally, participants will be subsequently divided into two groups based on their score on the APFT (score ranging from 1 to 5). Thus, the higher-scoring group (HSG) is defined as an APFT score of ≥ than 4; and the lower-scoring group (LSG) is defined as an APFT score of ≤ than 2.

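### The primary comparison of the three fitness tests is specified as One-Way ANOVA although the same participants do all three; read literally, it ignores the pairing and loses power for small to moderate differences.

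*Protocol article*

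**What the plan says.** The abstract sets the status of the comparison: "The primary analysis will assess differences in key physiological outcomes between the different CRF tests (TR vs. 2_MR_ vs. 30-15_IFT" and so on. The Study design section gives the design: "This is a randomized cross-over study using a within-subjects test-retest design". Each participant does the treadmill test, the 2-mile run and two 30-15IFT runs: "Participants will be instructed to visit the laboratory four times at least 72 h apart". The Participants section gives 32 people.

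The Statistical analysis section names the method for this comparison: "Differences in key physiological outcomes between the different CRF tests (TR vs. 2_MR_ vs. 30-15_IFT_) will be assessed by One-Way ANOVA analysis". No repeated-measures qualifier is attached. The next part of that section does plan a repeated-measures General Linear Model with test as the within-subject factor, but for the question of higher-scoring against lower-scoring participants on the Army Physical Fitness Test (APFT). The significance level for all analyses is p ≤ 0.05.

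**The concern.** The stated method does not match the stated design. One-Way ANOVA assumes that the values under each test come from different people. Here every person supplies a value under all three tests, and fit people will tend to do well on all of them. The design removes that person-to-person variation from the comparison; an independent-groups analysis puts it back into the error term. The rejection rate when there is no difference then falls well below 5%, and real small to moderate differences are missed.

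The direction matters in a validity study. The Introduction hypothesises that the 30-15IFT is a valid measure of cardiorespiratory fitness. A non-significant difference from the treadmill test could be read as agreement when it only reflects an insensitive test.

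**Working it through.** **The plan's own figure.** The only sample-size figure is 6 subjects, for the ICC aim (ICC 0.80, power 0.90, two-sided α 0.05, four observations). With an assumed null ICC of 0, C₀ = 1/(1 + 4 × 0.8/0.2) = 1/17, and n = 1 + 2(1.960 + 1.282)² × 4 / [(ln 17)² × 3] = 4.49, so 5. The stated 6 is close to this. It says nothing about power for the three-test comparison, for which the article gives no effect size, SD or correlation.

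**Inputs.** From the article: n = 32, k = 3 tests, α = 0.05. Assumed: one value per test and person, equal variances, equal correlation ρ between tests, and one test shifted by d between-person SDs from the other two. The article calls correlations of 0.68 or more high, so values of 0.7 and above are relevant if the tests agree as hoped; lower values are shown too.

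**Why the One-Way test is conservative.** With no difference between tests, the between-test mean square has expectation σ²(1 − ρ). The One-Way error mean square (df 3 × 31 = 93) has expectation σ². The repeated-measures error mean square (df 2 × 31 = 62) has expectation σ²(1 − ρ), which is the right comparator. For a pairwise difference, the true standard error is √[2σ²(1 − ρ)/n] and the One-Way analysis uses √(2σ²/n). The ratio 1/√(1 − ρ) is 1.4 at ρ = 0.5, 1.8 at 0.7 and 2.2 at 0.8.

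**Rejection rates by simulation** (20,000 runs per cell, One-Way vs repeated measures):

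| ρ | d = 0 | d = 0.3 | d = 0.4 | d = 0.5 | d = 0.7 |
|---|---|---|---|---|---|
| 0.5 | 0.4% vs 5% | 10% vs 39% | 25% vs 62% | 47% vs 82% | 87% vs 98% |
| 0.7 | under 0.1% vs 5% | 5% vs 59% | 18% vs 85% | 43% vs 97% | 91% vs 100% |
| 0.8 | about 0% vs 5% | 2% vs 77% | 13% vs 96% | 41% vs 100% | 93% vs 100% |

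At ρ = 0.3 and d = 0.4 the figures are 29% vs 47%. At ρ = 0.9 they are 0.6% vs 98% for d = 0.3, 38% vs 100% for d = 0.5 and 97% vs 100% for d = 0.7.

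**Check on one cell.** The repeated-measures noncentrality is λ = n(2d²/3)/(1 − ρ). For d = 0.4 and ρ = 0.5, λ = 32 × 0.1067/0.5 = 6.83; with df 2 and 62 this gives power 0.62, as simulated.

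**Shift detectable with 80% power.** One-Way: about 0.65, 0.63 and 0.62 SD at ρ = 0.5, 0.7 and 0.8. Repeated measures: 0.49, 0.38 and 0.31 SD.

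**Does the later model cover it?** The higher-scoring group is APFT ≥ 4 and the lower-scoring group APFT ≤ 2, on a scale of 1 to 5. Anyone scoring between 2 and 4 is in neither group, so that model gives a paired test effect only in the participants who fall into a group, not in all 32.

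**The case against.** The strongest reply is that One-Way ANOVA is loose shorthand for a one-factor repeated-measures ANOVA. The authors plainly know that test is a within-subject factor, because they call it that in the group model. This stands as a possibility. Equally, they wrote repeated-measures for one analysis and left it out for the primary one. The text settles neither reading, and a primary analysis should not depend on a guess.

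Four stronger readings are tempting, and the article does not support them.

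- A reader might infer that the One-Way test will nearly always find no difference. That holds only for no shift, or for shifts up to about 0.3 SD with ρ of 0.5 or more. At 0.5 SD it still rejects in about 38 to 47% of runs, and at 0.7 SD in about 87 to 97%.
- A reader might take the planned variance check ("the homogeneity of variances of normally distributed variables will be tested", by Levene's test) as proof of an independent-groups analysis. It is listed as a general check, is not tied to this comparison, and has a proper use for the two APFT groups.
- A reader might say that the plan is built to favour the authors' hypothesis. No passage says that a non-significant ANOVA will count as validity; the correlations between tests, which have stated magnitude thresholds, carry that aim. Only the conditional form stands: a missed difference could be read that way.
- A reader might see a conflict between interval and test, since the plan says "All data will be presented as mean ± SD with 90% confidence interval limits" and tests at 0.05. That sentence concerns the presentation of data. Nothing says that it is the interval for between-test differences.

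**Conclusion.** The concern stands in a limited form. As written, the primary analysis is an independent-groups method applied to paired data, and no other planned analysis makes the comparison in all 32 participants. Read literally, it cuts power for a 0.4 SD shift from 62% to 25% at ρ = 0.5 and from 96% to 13% at ρ = 0.8, with a smaller loss (47% to 29%) at ρ = 0.3. For shifts of 0.7 SD or more the choice seldom changes the result. The shift and the correlation are assumptions, as is equal correlation between tests. If the authors mean a repeated-measures ANOVA, only the wording is at fault. Because this is the primary analysis, it should be corrected before the data are analysed.

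**What to change.** In the Statistical analysis section, replace One-Way ANOVA with a one-factor repeated-measures ANOVA, or a linear mixed model with a random participant effect, with test as the within-subject factor and all 32 participants included. Report the paired between-test differences with confidence intervals from that model. The cost is a change of wording: no extra data or visits are needed, the group comparison already plans a model of this type, and the software named in the article is already to be used for it.

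### The declaration of good reliability rests on a consistency ICC, so a systematic shift between the two 30-15IFT trials does not enter it; SEM is also misnamed in the same section

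*Protocol article*

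**What the plan says.** All of the text at issue stands in one paragraph of the Statistical analysis section.

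- Relative reliability between the two 30-15IFT trials is "estimated using the ICC, two-way random effects model (consistency type".
- The decision rule reads: "The following criteria will be used to declare good reliability: CV < 5% and ICC > 0.69".
- The next sentence says that "the standard error of the estimate (SEM) and the coefficient of variation (CV) will be calculated as measures of absolute reliability", and describes these measures as "indicating the within-subject variation, as previously proposed".
- After that, "bias and random error will be calculated, followed by the minimal detectable change (MDC". No MDC formula is given.
- Usefulness is judged by "comparing the smallest worthwhile change (SWC) with the typical error of measurement (TE".
- The section opens by planning 90% confidence limits for the data presented.

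**The concern.** A consistency ICC removes the mean difference between trials before it compares participants. If everyone runs one or two stages further on the second attempt, through learning, or less far, through fatigue, the ICC does not move. The bias estimate would show this, but nothing in the rule refers to it.

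This matters because the scores are meant to be used at face value. The Introduction proposes MRS_IFT for prescribing and monitoring training, and the 30-15 Intermittent fitness test section converts it to VO2max by formula. High reliability of the test is also part of the study's main hypothesis. The declaration could therefore be made for a score whose agreement from one occasion to the next falls short of the plan's own threshold.

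A smaller point of wording goes with it. The standard error of the estimate is a regression quantity. Absolute reliability and the MDC rest on the standard error of measurement.

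**Working it through.** **Inputs.** From the protocol article: consistency ICC, thresholds ICC 0.69 and CV 5%, two 30-15IFT trials, n = 32, target ICC 0.80, stage step 0.5 km/h, ages 18-40, and the VO2max formula. Not in the document, so assumed: between-participant SD of MRS_IFT 1.0-1.5 km/h and mean 15-18 km/h.

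**The plan's own ICC figure.** The only one is the minimum sample of 6. Assuming a null ICC of 0, n = 1 + 2(zα+zβ)²k/[(ln C)²(k−1)], with C = 1/(1+k·0.80/0.20). For k = 4, two-sided 0.05 and power 0.90, this gives 4.49, so 5; an exact F test also gives 5, close to the stated 6. With the two trials actually analysed it is 10 (exact test 11), well below 32. The sample size does not bear on this point.

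**1. Effect of a shift on the ICC.** Write each score as participant + trial + error.

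- Consistency ICC = σ²(participant)/[σ²(participant)+σ²(error)].
- The agreement ICC adds σ²(trial) to the denominator.
- For two trials whose means differ by b observed SDs, σ²(trial) = b²/2 in units of SD².
- So agreement ICC = consistency ICC/(1+b²/2).

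| Shift b (SD) | Consistency ICC 0.80 | Consistency ICC 0.90 |
|---|---|---|
| 0.25 | 0.78 | 0.87 |
| 0.5 | 0.71 | 0.80 |
| 0.7 | 0.64 | 0.72 |
| 1.0 | 0.53 | 0.60 |

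A simulation with consistency ICC 0.90 and a 1 SD shift returned 0.90 and 0.60.

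**2. Where the verdict changes.** Setting the agreement ICC to 0.69 gives b = √[2(ICC/0.69 − 1)].

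- ICC 0.80: √(2 × 0.159) = 0.56 SD.
- ICC 0.90: √(2 × 0.304) = 0.78 SD.

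**3. In test stages (assumed SD 1.0-1.5 km/h).**

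- One stage, 0.5 km/h, is 0.33-0.5 SD. The agreement ICC is 0.76-0.71 from 0.80 and 0.85-0.80 from 0.90. All exceed 0.69.
- Two stages, 1.0 km/h, is 0.67-1.0 SD. It is 0.65-0.53 from 0.80, and 0.74-0.60 from 0.90.

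**4. Does the CV criterion catch it?** Its formula is not stated, so take both versions, with assumed SD 1.0 km/h, ICC 0.80, shift 0.7 km/h and mean 15-18 km/h.

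- Typical-error CV: √0.20 = 0.447 km/h, or 2.5-3.0%.
- CV from each participant's two scores, which includes the shift: √(0.20 + 0.7²/2) = 0.667 km/h, or 3.7-4.4%.

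Both are below 5%, so the declaration is made with an agreement ICC of 0.64.

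**5. Size on the VO2max scale.** The formula's slope on MRS_IFT is 1.03 + 0.058 × age: 2.07 at age 18 and 3.35 at age 40. A 1 km/h shift therefore moves estimated VO2max by about 2.1-3.4 ml/kg/min, against the 2.1 ml/kg/min plateau criterion in the treadmill section.

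**6. SEM and MDC.** SEM = SD√(1−ICC). The regression quantity, with correlation equal to the ICC, is SD√(1−ICC²). The ratio is √(1+ICC): 1.34 at 0.80 and 1.38 at 0.90. An MDC built on the regression quantity would be too large by the same factor.

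**The case against.** The plan labels the consistency ICC as relative reliability, for which it is a legitimate choice, and estimates absolute reliability and bias separately. A reader might infer that a systematic shift is ignored in the analysis. It is not: it will be estimated, and 90% limits are planned. What stands is narrower: the declaration is made without it.

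Nothing in the document suggests a large shift. The Study design section has familiarisation with the procedures at the first visit and at least 72 h between visits, and the Participants section bars strenuous activity during the study. These limit fatigue in particular but do not exclude learning, since no practice run is described. It is also true that a one-stage shift does not change the verdict at ICC 0.80 or above under the assumed SDs.

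A reader might also infer that the CV criterion is blind to a shift. That depends on a formula the article does not give: a typical-error CV ignores a shift, while a CV from each participant's two scores partly includes it.

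On SEM, it is tempting to say that the reliability rule uses the wrong quantity and that the MDC will be a third too large. The documents do not support this. SEM is not part of the rule, no MDC formula is printed, the same sentence gives SEM the meaning of within-subject variation, and the typical error of measurement is named correctly elsewhere. A slip in the name is the likelier reading.

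**Conclusion.** The point holds for the declaration. The ICC type and the rule are both printed, and together they allow good reliability to be declared when the agreement ICC is below 0.69. This needs a shift above about 0.56 SD at a consistency ICC of 0.80, or 0.78 SD at 0.90. Under the assumed SDs, that means roughly two stages, not one; with no SD in the document, the translation into km/h stays uncertain.

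The SEM wording is an error of naming. The 34-38% excess in the MDC is conditional on the regression quantity actually being computed.

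A reader might infer that the rule must also require a lower confidence limit above 0.69, since at n = 32 an observed ICC of 0.70 passes with a 90% CI of 0.51-0.82. The imprecision is real and should be visible, but that requirement does not follow. The observed ICC would have to reach about 0.84 (95% interval) or 0.82 (90%). At a true ICC of 0.80, the plan's own target, this would happen only about 28% or 39% of the time.

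**What to change.** - Base the declaration on the two-way random absolute-agreement ICC and show the consistency ICC beside it.
- Next to the declaration, report the mean difference between trial 1 and trial 2 and the ICC, each with the plan's 90% CI. Do not make a lower limit above 0.69 a condition.
- Replace the expansion of SEM with standard error of measurement, defined as SD of the trial differences/√2, and state MDC = 1.96·√2·SEM.

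The cost is one SPSS option and a few words, on data already to be collected. The downside is small: where there is a shift, the agreement ICC will be lower than the consistency ICC, so the declaration becomes somewhat harder to reach.

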## Strengths and limitations of this study

–This study will be the first to investigate the reliability and validity of the 30-15 Intermittent Fitness Test in military personnel.–This study will be the first to compare three different protocols for assessing cardiorespiratory fitness assessment in military personnel.–The study will provide the adopted formula for accurate estimation of maximal oxygen uptake (VO_2_max) for infantry members of the Slovenian Armed Forces (SAF) from the 30-15 Intermittent Fitness test.–The study will provide information about differences in visual attention between better and less physically prepared members of military personnel and its corresponding response following maximal endurance running test. This will enable better understanding of the importance of physical fitness for cognitively demanding situations like those at the battlefield.–A potential limitation of the study is that we will recruit greater number of male than female SAF members, as it is difficult to find an adequate number of female participants who meet the pre-specified inclusion criteria.

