### Participants

Thirty-two SAF infantry members (males, *N* = 27) will be recruited for the proposed study. Inclusion criteria are: age 18–40 years, both male and female SAF infantry members who are performing regular military tasks on daily basis, with no history of injuries in the last 6 months prior to recruitment, have not reported any musculoskeletal pain, with no history of chronic musculoskeletal, metabolic, pulmonary, neurological and cardiovascular diseases. Participants will be instructed to avoid any strenuous physical activity for at least 3 days prior to the start of the first testing session and during the course of study, which will be monitored by their superiors. They will be requested to refrain from consuming ergogenic substances and caffeinated beverages prior to the tests. Before the initial assessment on each testing day, a brief meeting will be held to explain the study protocol in detail.

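### Validity of 30-15IFT VO2max rests on Pearson's r plus tests of mean difference; no individual agreement or prediction error against the treadmill is planned

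*Protocol article*

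**What the plan says.** The last paragraph of the Introduction hypothesises that the 30-15IFT will be a highly reliable and valid measure of cardiorespiratory fitness. Strengths and limitations goes further: "The study will provide the adopted formula for accurate estimation of maximal oxygen uptake (VO_2_max) for infantry members". The Introduction treats the incremental treadmill run as the reference method for VO2max, and the 30-15 Intermittent fitness test section calculates VO2max from an existing formula using sex, age, body mass and final running speed.

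Under Statistical analysis, three elements bear on validity:

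- **Correlation.** "Relationship between VO_2max_, HR_peak_ and end running speed of 30-15_IFT_, TR, and 2_MR_ will be assessed using" Pearson's r. For VO2max across the three tests the article adds: "Also, the relationship between VO_2max_ obtained from TR, 2_MR_, and 30-15_IFT_ will be investigated". The size of r is graded "weak ≤ 0.35; 0.36 ≤ moderate < 0.67; 0.68 ≤ high < 1".
- **Mean differences.** Differences in key physiological outcomes between treadmill, 2-mile run and 30-15IFT "will be assessed by One-Way ANOVA analysis". The Abstract calls this comparison the primary analysis.
- **Repeated-measures model.** A general linear model takes test as within-subject factor and APFT group (HSG or LSG) as between-subject factor.

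Bias, random error, SEM, CV and minimal detectable change are also planned, but as reliability measures for the two 30-15IFT trials. The article expands SEM as the standard error of the estimate, yet uses it for within-subject variation between trials, not for error against the treadmill.

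**The concern.** A claim of accurate estimation concerns individuals: how far is this soldier's 30-15IFT VO2max from what the treadmill would have given? That needs the mean bias, the spread of individual differences and some check that the error does not change with fitness level. Pearson's r supplies none of these. A test of mean difference addresses only the first, and indirectly, because failing to reject equality is not evidence of agreement.

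The risk is practical. The 30-15IFT value comes from an existing formula, and a formula carried into another population may be offset or mis-scaled without lowering r. The article wants the test used to determine and monitor the readiness of infantry members, which is an individual-level use. A high r could then be published in support of accuracy that was never measured.

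**Working it through.** **The plan's own figure.** The article gives no validity figure to reproduce. Its one calculated figure, a minimum of 6 subjects, concerns the reliability ICC. The usual formula, n = 1 + 2(z_α + z_β)²k / [(ln C)²(k − 1)], with k = 4, ICC 0.80, power 0.90, two-sided α 0.05 and an assumed null ICC of 0, has C = 1/(1 + 4 × 0.80/0.20) = 1/17. It gives 1 + 2 × 10.51 × 4 / (8.03 × 3) = 4.49, so 5, close to the stated 6. It says nothing about validity.

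**Inputs from the article:** high from r = 0.68; 32 participants, 27 of them men, so 32 − 27 = 5 women. **Assumed:** the SD of VO2max, shown for 4, 5 and 6 ml/kg/min, equal for both methods.

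**1. What r cannot see.** For any a and any b > 0, corr(X, a + bY) = corr(X, Y). A constant or proportional error in the formula leaves r unchanged.

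**2. Individual disagreement at a given r.** With equal SDs, the SD of the differences is SD × √[2(1 − r)], so the 95% limits of agreement around any bias are ±1.96 × SD × √[2(1 − r)].

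- r = 0.68: 1.96 × √0.64 = 1.568, so ±1.57 SD.
- r = 0.90: 1.96 × √0.20 = 0.877, so ±0.88 SD.

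| Assumed SD (ml/kg/min) | r = 0.68 | r = 0.90 |
|---|---|---|
| 4 | ±6.3 | ±3.5 |
| 5 | ±7.8 | ±4.4 |
| 6 | ±9.4 | ±5.3 |

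Recalibration would not remove this. Around a fitted regression line the 95% error is ±1.96 × SD × √(1 − r²). At r = 0.68 that is ±1.44 SD, or ±5.7, ±7.2 and ±8.6 for the same SDs.

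**3. Precision of r.** Fisher's z for 0.68 is 0.829, with SE 1/√29 = 0.186. Then 0.829 ± 1.96 × 0.186 back-transforms to 0.43 to 0.83 (90%: 0.48 to 0.81). The interval reaches well into the moderate band.

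**4. What the tests of means add.** In a simulation of 5,000 runs (n = 32, SD 5, r = 0.68 between all tests, bias in one test only), a bias of 2 ml/kg/min was detected in about 19% of runs by one-way ANOVA, which ignores pairing, and in about 82% by repeated-measures ANOVA. For a bias of 3 the figures were about 72% and over 99%. So the plan can detect mean bias, well or poorly depending on the model. Neither model estimates individual error.

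**5. Pooling the sexes.** With p = 5/32, p(1 − p) = 0.132. If both methods show the same sex gap d, pooled r = (r·SD² + 0.132d²)/(SD² + 0.132d²). Take an assumed within-sex r of 0.60, gap of 6, 8 or 10 and within-sex SD of 4, 5 or 6. Pooled r then runs from 0.65 to 0.78 and reaches 0.68 in 6 of 9 combinations. At gap 8 and SD 5: (15 + 8.44)/(25 + 8.44) = 0.70.

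**The case against.** The strongest reply is that the plan does look at bias. The comparison of means is called the primary analysis, and the repeated-measures model gives a paired test of the same means. That stands: a reader might infer that validity is judged by r alone, or that bias is ignored, and the article does not support either statement. The reply does not reach individual error, however. The repeated-measures model is also framed around groups defined by APFT scores of at least 4 and at most 2, so as described it has no place for scores in between.

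Second, the cut-offs for r grade the size of a correlation. A reader might infer that r of 0.68 or more triggers a declaration of validity, but no such rule is written; the only declaration rule (CV and ICC) is for reliability.

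Third, ±8 ml/kg/min is tempting as a headline, but it needs an SD of about 5, which the article does not give. SDs of 3 to 8 give ±4.7 to ±12.5. The sex-pooling figures are likewise assumed, and recruiting both sexes does not make a pooled r an error.

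Fourth, a reader might take the promised adopted formula to be a new infantry equation that no analysis fits. It may equally mean the existing formula taken into use, and the text does not settle this. Nor is it explicit which 30-15IFT VO2max enters the comparison, since a portable gas analyser is listed for physiological parameters while the 30-15IFT section uses the formula.

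Finally, this is not detail that a condensed article merely leaves out. The section sets the validity method down to the cut-offs and applies error measures to the retest comparison but not to the treadmill comparison.

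**Conclusion.** The concern holds in this form: correlation and tests of mean difference are planned, but no individual-level agreement or prediction error against the treadmill, so the planned analyses cannot support the promise of accurate estimation. The size in general terms is limits of about ±1.57 SD at the lower edge of the high band, and ±0.88 SD even at r = 0.90. In ml/kg/min this is ±6.3 to ±9.4 and ±3.5 to ±5.3 for assumed SDs of 4 to 6, with equal SDs on both methods and any bias added on top. The logical gap does not depend on those assumptions; only the figures do. The plan should be changed, but the defect lies in the analysis and not in the data to be collected.

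**What to change.** In Statistical analysis, add for VO2max:

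1. A Bland-Altman comparison of 30-15IFT VO2max (existing formula, first 30-15IFT trial) with treadmill VO2max: mean bias, 95% limits of agreement and slope of the difference on the mean, each with a confidence interval. State that the formula value is the one being validated.
2. The formula's standard error of estimate against the treadmill.
3. r with its confidence interval and, as a sensitivity analysis, r adjusted for sex (27 men, 5 women).
4. A statement of what the adopted formula means. If a new infantry equation is intended, fit it to treadmill VO2max and report its leave-one-out error beside that of the existing formula. If not, limit the claim to the tested error of the existing formula.

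The cost is a few hours of analysis and rewording, with no new measurements or participants. The downside is that the validity statement may turn out less favourable than a correlation alone would suggest.
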